## Abstract

**Background:**

Laminoplasty and laminectomy have been used for decades for the treatment of intraspinal space-occupying lesions, spinal stenosis, disc herniation, injuries, etc. After these procedures, patients often experience severe postoperative pain at the surgical site. Intense immediate postoperative pain after many spinal procedures makes its control of utmost importance. Preemptive injection of local anesthetics can significantly reduce postoperative pain during rest and movement; however, the analgesic effect is only maintained for a relatively short period of time. Whether betamethasone combined with local anesthetic for laminoplasty or laminectomy has better short-term and long-term effects than the local anesthetic alone has not been reported yet.

**Methods:**

The PRE-EASE trial is a prospective, randomized, open-label, blinded endpoint, single-center clinical study including 116 participants scheduled for elective laminoplasty or laminectomy, with a 6 months’ follow-up process. Preemptive local infiltration with betamethasone and ropivacaine (treatment group) or ropivacaine alone (control group) throughout the entire thickness of the planned incision site will be performed by the surgeon prior to making the incision. The primary outcome will be the cumulative butorphanol consumption within the first 48-h postoperative period.

**Discussion:**

This study will add significant new knowledge to the effect and feasibility of preemptive local infiltration of betamethasone for postoperative pain management in laminoplasty and laminectomy.

**Trial registration:**

ClinicalTrials.gov: NCT04153396. Registered on 6 November 2019.

## Administrative information

Note: the numbers in curly brackets in this protocol refer to Standard Protocol Items: Recommendations for Interventional Trials (SPIRIT) checklist item numbers. The order of the items has been modified to group similar items (see http://www.equator-network.org/reporting-guidelines/spirit-2013-statement-defining-standard-protocol-items-for-clinical-trials/).

## Introduction

### Background and rationale {6a}

Laminoplasty and laminectomy have been used for decades for the treatment of intraspinal space-occupying lesions, spinal stenosis, disc herniation, injuries, etc. After these procedures, patients often experience severe postoperative pain at the surgical site. With currently available systemic analgesics, the drug-related side effects may exacerbate when the drug concentration in the blood is high. However, when the blood concentration is low, there may be insufficient analgesia which may also lead to insufficient management of pain at movement [1]. Intense immediate postoperative pain after many spinal procedures makes its control of utmost importance [2]. Despite recent advancements in postoperative pain management, there is evidence of inadequate postoperative pain control after spinal surgery, which leads to reduced patient mobility [1, 2]. Early mobilization after spine surgery is vital for reduction of hospital stay and postoperative complications, and better performance-based functional tests and patient-reported outcome measures [3]

Severe immediate postoperative pain increases the risk of chronic pain along with the occurrence of nerve injury and the development of neuronal plasticity associated with peripheral and central sensitization [4]. Central sensitization, an increase in central nervous system excitability, occurs due to the ongoing noxious input [5], which leads to allodynia, the perception of pain resulting from a normally non-painful stimulus [6]. Therefore, reducing postoperative acute pain is vital for the prevention of chronic pain.

At present, several pain-controlling methods are available, with opioids being the cornerstone for management of severe acute postoperative pain [2, 7]. However, there are many compelling reasons to avoid opioids in surgical patients due to their numerous side effects [8]. Methods for systemic administration include oral analgesics, intermittent intravenous or intramuscular injections, and patient-controlled intravenous analgesia, etc. [1]. Nevertheless, the aforementioned methods may have many side effects, and are usually used after the occurrence of pain. Hence, the analgesic effects are sometimes inadequate.

Topical administration options have fewer systemic side effects. Preemptive injection of local anesthetics can significantly reduce postoperative pain, although the analgesic effect is maintained for a relatively short period of time. Incidences of technical failure or local anesthetic toxicity from wound catheters were found to be low in a study by Liu et al. [9], although other reports have raised concerns about probable wound infection from the existence of a catheter [10]. Furthermore, indwelling catheters come with a risk of complications such as prolapse or obstruction of the catheter. Cost-effectiveness, optimal site for catheter placement, and optimal dosage are also factors to be considered [9]. Techniques such as epidural analgesia and nerve blockade may have a possible high failure rate and not be cost effective, but they can deliver better postoperative analgesia [11–13]. Gurbet et al. [1] reported that preemptive infiltration of bupivacaine or levobupivacaine combined with methylprednisolone, a short-acting glucocorticoid, can effectively control pain after unilateral lumbar laminectomy. However, this solution has a shorter duration of action, and the study involved merely 24-h postoperative observation and only 60 participants. Ersayli et al. [14] reported that, compared to infiltration at wound closure, preemptive injection of bupivacaine or bupivacaine-methylprednisolone into muscles near the incisional site provided more effective analgesia after lumbar discectomy, and they concluded that methylprednisolone combined with local anesthetic was not superior to the analgesic effect of local anesthetic alone. However, in the study [14], 75 participants were enrolled with only 15 in each group. Therefore, it is necessary to observe more cases to explore other compatibilities of drugs with longer duration of action and stronger analgesic effect.

Betamethasone, a stereoisomer of dexamethasone, is a long-acting corticosteroid which has longer lasting anti-inflammatory properties because of its partial presence in particulate form in ropivacaine, acting as a local reserve [15]. Whether betamethasone combined with local anesthetic for laminoplasty or laminectomy has better analgesic effects than the local anesthetic alone has not been reported yet. Therefore, a detailed study is needed to compare the postoperative analgesic efficacy of preemptive infiltration of betamethasone plus ropivacaine and ropivacaine alone for laminoplasty or laminectomy.

### Objectives {7}

We hypothesize that preemptive local infiltration of betamethasone plus ropivacaine helps relieve postoperative pain, reduces the request for postoperative analgesics, and promotes early rehabilitation without significant risks.

### Trial design {8}

The PRE-EASE trial is a prospective, randomized, open-label, blinded endpoint (PROBE), single-center clinical study designed to compare the postoperative analgesic efficacy of preemptive wound infiltration of ropivacaine alone and betamethasone plus ropivacaine for laminoplasty or laminectomy. In total, 116 patients will be randomly assigned to the betamethasone-ropivacaine (treatment) group and the ropivacaine (control) group at a 1:1 ratio. The Consolidated Standards of Reporting Trials (CONSORT) patient flow diagram is presented in Fig. 1.

**Fig. 1 Fig1:**
[figure not shown]
CONSORT patient flow diagram of the PRE-EASE trial

## Methods: participants, interventions, and outcomes

### Study setting {9}

This is a single-center study which will be conducted from January 2021 to June 2022 at Beijing Tiantan Hospital, Capital Medical University, Beijing, China.

### Eligibility criteria {10}

#### Inclusion criteria

The inclusion criteria are as follows:
Patients scheduled for laminoplasty or laminectomyAmerican Society of Anesthesiologists (ASA) classification of I or IIAge 18 to 64 yearsParticipants with an anticipated full recovery within 2 h postoperatively.

#### Exclusion criteria

Potential participants will have to be excluded if they:
Refuse to participateCannot use a patient-controlled analgesia (PCA) device and cannot understand the instructions of a Visual Analog Score (VAS)Have previous history of spinal surgeryAre allergic to opioids, betamethasone, or ropivacaineHave peri-incisional infectionHave history of stroke or a major neurological deficitHave trauma, deformityHave psychological problemsHave extreme body mass index (BMI) (< 15 or > 35 kg/m^2^)Have history of excessive alcohol or drug abuse, chronic opioid use (more than 2 weeks), or use of drugs with confirmed or suspected sedative or analgesic effectsAre using systemic steroidsAre pregnant or breastfeedingHave preoperative Glasgow Coma Scale score < 15Have received radiation therapy or chemotherapy preoperatively, or with a high probability to require postoperative radiation therapy or chemotherapy according to the preoperative imagingAre not able to give written informed consent.

### Who will take informed consent? {26a}

Participants will be recruited from the neurosurgical outpatient department at Beijing Tiantan Hospital, affiliated to Capital Medical University, Beijing, China, by two research members from the department of neurosurgery. Based on the inclusion and exclusion criteria, patients will be screened for study participation. Patients scheduled for surgery who fulfill the eligibility criteria and express an interest in participating in the study will be visited by a research assistant, 1 day before the surgery, to obtain written consent. A verbal explanation of the written consent will be provided by the research member, and any questions regarding the study will be answered. Each participant will have sufficient time to decide whether to participate in this study. If patients are willing to participate, written consent will be obtained.

### Additional consent provisions for collection and use of participant data and biological specimens {26b}

On the consent form, participants will be asked if they agree to the use of their data, should they choose to withdraw from the trial. Participants will also be asked for permission for the research team to share relevant data with people from regulatory authorities, where relevant. This trial does not involve collecting biological specimens for storage.

### Interventions

#### Explanation for the choice of comparators {6b}

A total of 30 ml of solution will be prepared for each group, which will include 0.5 ml of compound betamethasone injection (Diprospan® betamethasone propionate 5 mg and betamethasone sodium phosphate 2 mg) added to 14.5 ml of saline and 15 ml of 1% ropivacaine (NaiLePin®10 mg/ml, AstraZeneca AB, Södertälje, Sweden) for the treatment group and 15 ml of ropivacaine added to 15 ml of saline for the control group [15, 16]. The study investigator will be responsible for preparing the respective drugs to be used for preemptive infiltration in these two groups, and the neurosurgeon will infiltrate the planned incision site with the respective study solution, prior to the incision.

### Intervention description {11a}

#### Preemptive infiltration

A 10-cm-long 22-gauge needle will be introduced into the planned incision site by the surgeon, to infiltrate the prepared solution. A total of 10 ml of solution will be injected into each level. The total volume of solution to be injected will be based on the number of levels to be treated, will be consistent in every participant, and will be recorded by the investigator. The study solution will be injected into the subcutaneous tissue and paravertebral muscles, along with the posterior area around the spinous process, lamina, transverse process, and the facet joints, along both sides of the planned incision. The epidural space and intrathecal space will not be infiltrated. The local infiltration solution in the treatment group will consist of betamethasone and ropivacaine with saline, whereas ropivacaine alone will be used with saline in the control group. All other aspects of the rehabilitation process will be identical between the two groups.

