#### Additional interventions

The ongoing continuous infusion of propofol and remifentanil will be stopped right after the suture of the incision. To prevent postoperative nausea and vomiting, 8 mg of ondansetron will be administered. Any residual muscle relaxation will be antagonized by atropine and neostigmine. Once the patient is hemodynamically stable, along with the recovery of adequate spontaneous ventilation and satisfactory neurological evaluations, the patient will be extubated and transferred to a post-anesthesia care unit. A PCA device containing 10 mg butorphanol tartrate injection (HengRui Medical Co., Ltd., Lianyungang, Jiangsu, China) and 10 mg tropisetron hydrochloride injection (Southwest Pharmaceutical Co., Ltd., Chongqing, China) diluted to a total volume of 100 ml with 0.9% normal saline, will be connected to the patients, for a total duration of 48 h. Apon® electronic infusion pumps (ZZB-I-150, Apon Medical Technology Co., Ltd., Jiangsu, China) will be used for patient-controlled analgesia (PCA). The PCA device will have a bolus dose of butorphanol set at 0.3 mg with a lockout interval of 15 min. Both the initial dose and background infusion of the PCA device will be set at zero. The participants will be advised to push the analgesic demand button when they feel pain. Each press will be recorded by an electronic memory system, including both valid and invalid presses. Invalid presses refer to presses for bolus during the lockout period. In case of inadequate analgesia four times after the butorphanol bolus, the bolus dose would be increased gradually with the final maximum dose not exceeding 4 mg per hour. There will be real-time updates of drug dosage, press counts, and time of each press to the iPainfree online recording system. Participants will be allowed to take oral supplementary acetaminophen 500–1000 mg every 4 to 6 h if necessary after 48 h, until the end of our study.

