### Outcomes {12}

Clinical and demographic characteristics such as gender, age, weight, BMI, ASA status, type of surgery (laminoplasty or laminectomy), level of spine to be treated (cervical, thoracic, lumbar, or sacral), number of levels to be treated (1, 2, 3, 4 levels or more than 4 levels), and Oswestry Disability Index (ODI) will be recorded. After the operation, the duration of surgery, length of incision (in millimeters), and volume of local anesthesia (in milliliters) injected for preeemptive infiltration will be recorded. Postoperative complications such as postoperative pain due to spinal cord or nerve injury, wound infection, wound hematoma, delirium, serious adverse effects, and death may affect the follow-up process. Other complications such as allergic reaction, local or systemic toxicity, changes in wound healing, or increased wound drainage will be closely monitored.

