### Statistical methods

#### Statistical methods for primary and secondary outcomes {20a}

Statistical analyses will be performed using the statistical package SPSS software 25.0. A Kolmogorov-Smirnov test will be used to assess normality of variables. Data for normal distribution will be presented as mean ± SEM (standard error of the mean). Variables for skewed distributions will be described as median and interquartile range (IQR). Categorical variables will be expressed as frequencies with percentages.

Comparisons between the groups will be carried out using an independent *t* test to compare normally distributed data, the Mann-Whitney *U* test for skewed data, and a χ^2^ test or Fisher’s exact test to compare categorical data such as safety analyses with the incidence of AEs. For numerical data collected at different time points throughout the course of 6 months (e.g., PCA cumulative consumption of butorphanol, PONV, RSS, PSS, and ODI), repeated measures analysis of variance will be performed between the two groups. The significance level will be set at *P* < 0.05.

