## Discussion

This trial will be a PROBE study. It will have better application in routine clinical practice, along with the clinical outcomes of a large simple research, which will permit a broader patient population and will include the advantage of randomization and an extensive evaluation of endpoints by blinded experts [19]. To our knowledge, there has been no attempt in the past to infiltrate laminoplasty or laminectomy with a preemptive local administration of betamethasone and ropivacaine. This study will add significant new knowledge to the effect and feasibility of preemptive wound infiltration of betamethasone.

Due to its large particles occluding the blood vessels supplying the spinal cord, betamethasone was previously reported to result in infarction of spinal cord after epidural analgesia [20]. However, we speculate that local peri-incisional infiltration of betamethasone is safe, as betamethasone has previously been used for intralesional [21], local infiltration [22], intramuscular [23], and intra-articular injections [16]. Local infiltration of steroid hormones will undeniably present the risk of delayed wound healing or local infection. However, we intend to use the lowest possible concentration of betamethasone for local infiltration based on the previous literature [15, 16, 22, 24], and thus this concentration should be considered safe. Wound healing and infection will be closely observed. The study will be immediately terminated in case of serious adverse reactions by the PRE-EASE Trial Management Group.

There are still some limitations regarding our study. Firstly, this is a single-center study; a multicenter study would be helpful in providing more significant data. In addition to incisional pain, acute pain after laminoplasty or laminectomy may be followed by long-term chronic pain that may not only originate from the incisional wound, but may also include neuropathic pain from spinal cord damage and nerve root injury. Another possible limitation of this study is that it will only involve infiltration of the surrounding tissue of the incision site. Therefore, we would like to suggest a further detailed study, regarding whether local betamethasone injection into the affected nerve roots before closure could be beneficial for postoperative pain after laminoplasty or laminectomy.

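### At four or more levels the 30 ml preparation and the 10 ml per level rule cannot both be followed, and no maximum infiltration dose is stated

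*Protocol article*

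**What the plan says.** **Volume prepared.** Under Explanation for the choice of comparators {6b}: "A total of 30 ml of solution will be prepared for each group". Both arms receive 15 ml of 1% ropivacaine. The treatment arm has 0.5 ml of compound betamethasone made up with saline; the control arm has saline only. The strength is given as "betamethasone propionate 5 mg and betamethasone sodium phosphate 2 mg", without saying whether this is the content of 1 ml or of the 0.5 ml used.

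**Volume injected.** Under Preemptive infiltration: "A total of 10 ml of solution will be injected into each level", and "The total volume of solution to be injected will be based on the number of levels to be treated". The same sentence goes on to call this volume consistent across participants.

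**Levels expected.** Outcomes {12} records at baseline the "number of levels to be treated (1, 2, 3, 4 levels or more than 4 levels". Neither the inclusion nor the exclusion criteria limit the number.

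**Safety argument.** The Discussion relies on using the lowest possible betamethasone concentration, "and thus this concentration should be considered safe". It does not address total dose. For butorphanol, by contrast, Additional interventions does set a ceiling, "with the final maximum dose not exceeding 4 mg per hour".

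**Analysis.** Statistical methods {20a}: "Comparisons between the groups will be carried out using an independent" t test for normal data, or a Mann-Whitney test for skewed data. No covariate is named. Additional analyses {20b} gives gender, age, weight and type of surgery as examples of subgroup factors.

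**Acetaminophen after 48 h.** Additional interventions and section {11d} allow 500–1000 mg at 4- to 6-hour intervals. Section {11c} gives a 6-hour interval. No daily maximum appears.

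**The concern.** The two dosing statements agree for one to three levels and conflict from four levels upward, in patients the protocol itself expects to enrol. Whoever prepares or injects the solution must then choose between mixing more, spreading 30 ml more thinly, or diluting it. These choices give different total doses, volumes per level or concentrations.

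Two things are at stake. First, if more is mixed, the patients with the most extensive surgery receive the largest amounts of depot steroid and local anesthetic, with no stated bound. The Discussion's safety argument does not cover this, because concentration stays constant while the amount rises. Second, the trial is open-label apart from pain evaluators, outcome assessors and analysts. A choice improvised at the table can therefore be made by someone who knows the arm. That is a risk to a uniform intervention, not a demonstrated bias.

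A secondary point is that number of levels sets the dose, reflects surgical extent and is already recorded, yet the stated primary comparison makes no use of it.

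**Working it through.** **1. Sample size (Sample size {14}).** Inputs: means 120 and 70 mg, SDs 90 and 50 mg, two-sided α 0.05, 90% power, 20% dropout.
- With 46 per arm, SE = √((90² + 50²)/46) = 15.18 mg. Welch power for a 50 mg difference is 90.1%; with 45 per arm it is 89.5%.
- 46/0.8 = 57.5, so 58 per arm and 116 in total.

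The stated figure is reproduced, and nothing below changes it.

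**2. Concentration of the preparation.**
- Ropivacaine: 15 ml × 10 mg/ml = 150 mg in 30 ml, or 5 mg/ml.
- Betamethasone product: 0.5 ml in 30 ml, or 0.0167 ml per ml.

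**3. Dose if 10 ml per level is kept at that concentration.** Volume = 10 ml × levels.

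| Levels | Volume (ml) | Ropivacaine (mg) | Betamethasone product (ml) | Betamethasone (mg), 7 mg per 1 ml | Betamethasone (mg), 7 mg per 0.5 ml |
|---|---|---|---|---|---|
| 1 | 10 | 50 | 0.17 | 1.2 | 2.3 |
| 2 | 20 | 100 | 0.33 | 2.3 | 4.7 |
| 3 | 30 | 150 | 0.50 | 3.5 | 7.0 |
| 4 | 40 | 200 | 0.67 | 4.7 | 9.3 |
| 5 | 50 | 250 | 0.83 | 5.8 | 11.7 |

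The betamethasone columns apply to the treatment arm only. The last two show the twofold uncertainty in the stated strength. The dose already rises between one and three levels; what changes at four is that the prepared volume no longer suffices (40/30 = 1.33 times; 50/30 = 1.67 times at five).

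**4. What staff could do at four levels.**

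| Choice | Total (ml) | Per level (ml) | Ropivacaine (mg/ml) | Ropivacaine (mg) |
|---|---|---|---|---|
| Mix more | 40 | 10 | 5 | 200 |
| Spread 30 ml | 30 | 30/4 = 7.5 | 5 | 150 |
| Dilute to 40 ml | 40 | 10 | 150/40 = 3.75 | 150 |

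The first breaks the 30 ml preparation, the second breaks 10 ml per level, and the third changes the concentration.

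**5. Adjusting for number of levels.** With N = 92 evaluable, common variance and p covariate terms, the variance relative to the unadjusted comparison is (1 − R²) × (1 + p/(N − p − 3)).
- One ordinal term: 1 + 1/88 = 1.011. Adjustment pays once R² exceeds 1 − 1/1.011 = 1.1%.
- Four indicators: 1 + 4/85 = 1.047. Break-even R² is 4.5%.

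The documents do not give R², the share of within-arm variance in butorphanol use explained by levels. A simulation used the protocol's means and SDs, 46 per arm, skewed residuals and assumed shares of 25/25/20/15/15% for 1, 2, 3, 4 and more than 4 levels. It gave these effective sample sizes relative to the unadjusted comparison:

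| Assumed R² | One ordinal term | Four indicators |
|---|---|---|
| 0% | 0.99 | 0.96 |
| 5% | 1.04 | 1.01 |
| 10% | 1.09 | 1.06 |
| 20% | 1.21 | 1.17 |

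Type I error with one term and HC3 standard errors was 4.8 to 5.3%. With assumed shares of 45/30/15/6/4%, one term gave 0.99/1.03/1.08/1.19.

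**6. Acetaminophen at 1000 mg around the clock.** Every 4 h: 24/4 × 1000 mg = 6 g per day. Every 6 h: 24/6 × 1000 mg = 4 g per day.

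**The case against.** The strongest reply is that 30 ml is the ceiling. The text speaks of infiltrating the prepared solution, that solution is 30 ml, and the volume is called consistent across participants. On that reading nobody exceeds 150 mg ropivacaine or 0.5 ml of betamethasone product. Alternatively, 30 ml is only a mixing recipe, and scaling volume to surgical extent is the intended design. Both readings are possible, so a rise to 200 or 250 mg is one branch of the conflict and not an established fact. But the first breaks 10 ml per level at four or more levels, and the second leaves the dose without a maximum. The consistency clause does not help, because a volume based on levels differs between patients.

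It is also fair that the protocol has safeguards: injected volume is recorded, local and systemic toxicity is monitored, and an independent committee reviews safety at each 25% of inclusions. These detect a problem; they do not settle the dose.

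On the analysis, the stated unadjusted test is valid, covariates are often left to an analysis plan that is not shown here, and the subgroup factors are given only as examples, so levels are not excluded. The gain from adjustment rests on an assumed R². All of that stands. Adjustment is therefore offered as an inexpensive improvement, not as the repair of an error.

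On acetaminophen, 6 g per day takes the largest dose at the shortest interval for a drug allowed only as needed, and it starts after the primary outcome has ended. The two intervals still differ.

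**Conclusion.** The dosing conflict is real and worth fixing: the stated preparation and the stated volume per level cannot both hold at four or more levels. The ambiguity at four levels is 150 against 200 mg ropivacaine, and at five levels 150 against 250 mg. The betamethasone amount carries a further factor of two from the unclear strength.

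A reader might infer that patients with many levels will be overdosed. The documents do not support that. They give no toxicity threshold and no share of patients with four or more levels, and they leave open whether more than 30 ml would ever be injected.

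A reader might also infer that the level-dependent dose biases the primary result. It does not: both arms follow the same volume rule and allocation is random. The sample size of 116 is unaffected.

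Not using number of levels costs at most some precision. How much depends on an R² that the documents do not give: from a loss of about 1% of effective sample size with adjustment at R² = 0 to a gain of about 9% at 10%. The acetaminophen discrepancy is minor and concerns only safety and outcomes after 48 h.

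**What to change.** 1. **Dosing rule.** State 10 ml per level up to a total of 30 ml, with the 30 ml spread over all levels when there are four or more (7.5 ml each at four, 6 ml each at five). Another ceiling in mg for ropivacaine and betamethasone, set by the clinical team, would serve as well. Remove or clarify the clause on consistency across participants, and give the betamethasone strength per ml.
2. **Primary comparison (optional but cheap).** Fit a linear model of 48-h butorphanol on arm and number of levels, with levels as one ordinal term scored 1 to 5 and HC3 standard errors. Fix this before outcome data are seen by arm. Keep the stated unadjusted test, including Mann-Whitney for skewed data, as a sensitivity analysis. One term is preferred to four indicators because it loses about 1% rather than 4% of effective sample size if levels are not prognostic.
3. **Acetaminophen.** Use the 6-hour interval of section {11c} in Additional interventions and section {11d} as well, and state a daily maximum.

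Items 1 and 3 are wording changes. Item 2 changes the primary analysis by one baseline term and moves the present test to a supporting role. No new data, visits or patients are needed, because levels and injected volume are already recorded.
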